## Abstract

**Introduction:**

Real-world data on COVID-19 vaccine effectiveness are needed to validate evidence from randomized clinical trials. Accordingly, this study aims to evaluate, in a real-world setting in Brazil, the effectiveness of Pfizer-BioNTech BNT162b2 against symptomatic COVID-19 and COVID-19-related complications across diverse populations.

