### Secondary objectives

The secondary objectives are to assess the impact of BNT162b2 on: (1) symptomatic SARS-CoV-2 infection caused by circulating variants (e.g., Delta, and Omicron); (2) duration of COVID-19 symptoms; (3) hospitalization for COVID-19; (4) need for ICU admission; (5) need for invasive mechanical ventilation; (6) death from COVID-19; (7) health-related quality of life; (8) persistent COVID-19 symptoms; and (9) symptomatic SARS-CoV-2 reinfection.

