### Outcomes

The primary outcome is symptomatic COVID-19, defined by the presence of at least one COVID-19-like symptom as listed in Participants section and confirmed by a positive RT-PCR result for SARS-CoV-2 infection from participants’ NP or nasal swabs.

Secondary outcomes are: (1) symptomatic SARS-CoV-2 infection associated with circulating variants (e.g., Delta, and Omicron); (2) duration of COVID-19 symptoms; (3) hospitalization for COVID-19 within 30 days from enrollment among patients with confirmed COVD-19; (4) need for ICU admission within 30 days from enrollment among patients with confirmed COVD-19; (5) need for invasive mechanical ventilation within 30 days from enrollment among patients with confirmed COVD-19; (6) death from COVID-19 within 90 days from enrollment among patients with confirmed COVD-19; (7) health-related quality of life at 90 days from enrollment among patients with confirmed COVD-19, measured by the three-level version of the EuroQol five-dimensional descriptive system (range, -0.17 [worst] to 1.0 [best]; minimal important difference, 0.03) [7, 8]; (8) persistent COVID-19 symptoms at 180 days from enrollment among patients with confirmed COVD-19; (9) symptomatic SARS-CoV-2 reinfection within 365 days from enrollment among patients with confirmed COVD-19, defined as recurrence of COVID-19-like symptoms confirmed by a positive RT-PCR or antigen test for SARS-CoV-2 more than 90 days after primary infection.

Safety data including adverse events and serious adverse events will be assessed upon inclusion of cases and controls and over the 12-month follow-up for cases, under the standard of care procedures for the city of Toledo’s surveillance program per Brazilian regulatory authority’s requirements.

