#### Secondary outcome analyses

The association between the exposition variables with symptomatic SARS-CoV-2 infection caused by circulating variants as well as the association between secondary exposition variables with symptomatic SARS-CoV-2 infection will be assessed using the same statistical model used for the primary outcome.

Crude and adjusted generalized linear models will be used to assess the impact of exposures on duration of COVID-19 symptoms, hospitalisation for COVID-19, need for ICU admission, need for invasive mechanical ventilation, death from COVID-19, health-related quality of life, persistent COVID-19 symptoms, symptomatic SARS-CoV-2 reinfection among participants with a positive RT-PCR result for SARS-CoV-2, and to test associations between length of time after receipt of the second or third dose of BNT162b2 and the risk of symptomatic SARS-CoV-2 infection, according to the probability distribution of each outcome. Quantitative outcomes will be expressed as mean difference. Categorical outcomes will be expressed as hazard ratio or relative risk as appropriate.

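### The severe outcomes are analysed only among test-positive cases, so they show progression after infection, while the abstract promises effectiveness against complications

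*Protocol article*

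**What the plan says.** All references are to the protocol article.

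- **Aim.** The Introduction part of the Abstract says the study will evaluate "the effectiveness of Pfizer-BioNTech BNT162b2 against symptomatic COVID-19 and COVID-19-related complications across diverse populations".
- **Objectives.** Secondary objectives begins "The secondary objectives are to assess the impact of BNT162b2 on" and lists hospitalisation, ICU admission, invasive ventilation and death without limiting them to infected people. The Discussion counts the follow-up of cases as a strength because it lets vaccine impact on complications be evaluated.
- **Outcome definitions.** Outcomes restricts each of these to confirmed cases: "hospitalization for COVID-19 within 30 days from enrollment among patients with confirmed COVD-19", "need for ICU admission within 30 days from enrollment among patients with confirmed COVD-19" and "need for invasive mechanical ventilation within 30 days from enrollment among patients with confirmed COVD-19". Death is restricted in the same way, at 90 days.
- **Analysis.** Secondary outcome analyses says "Crude and adjusted generalized linear models will be used to assess the impact of exposures on duration of COVID-19 symptoms, hospitalisation for COVID-19" and continues with the other severe outcomes. Categorical results are reported as hazard ratios or relative risks. The primary test-negative model is carried over only to variant-specific infection and to the secondary exposures.
- **Controls.** Data collection says that controls are assessed once, at baseline.
- **Limitations.** The Discussion raises confounding between vaccinated and unvaccinated people, but not the effect of conditioning on infection.

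**The concern.** Becoming a symptomatic case is something vaccination is expected to change; that is the primary hypothesis. A comparison made only among cases therefore starts after part of the vaccine's effect has already acted. Two things follow.

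1. Complications prevented because the person never became a case do not enter the contrast. What remains is the risk of progression given symptomatic infection for which care was sought.
2. Vaccinated people who became cases despite vaccination are compared with unvaccinated cases. The two groups may differ in unmeasured risk factors because vaccination influenced who entered the case group, so the contrast is open to selection bias.

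The practical risk lies in interpretation. A weak or null case-only relative risk, reported under an objective worded as impact on hospitalisation, invites the conclusion that the vaccine does little against hospitalisation. It may in fact prevent much of it by preventing the illness.

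**Working it through.** **Is the restriction really fixed in the article?** In the long sentence in Secondary outcome analyses, the limit to RT-PCR-positive participants could be read as attaching only to reinfection. Outcomes settles the matter, because each severe outcome is defined there among confirmed cases. Controls are not followed, which agrees. Population, model family and effect measure are all stated, so this is not a detail left to an unseen analysis plan.

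**Source of the 80%.** Sample size assumes effectiveness of 80% (odds ratio 0.20), 90% coverage in controls and two controls per case. Its figure reproduces:

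- Coverage in cases = 0.9 × 0.2 / (0.1 + 0.9 × 0.2) = 0.643.
- Var(ln OR) = [1/(0.643 × 0.357) + 1/(2 × 0.9 × 0.1)] / n.
- Setting the full 95% interval width, 2 × 0.2 × sinh(1.96 × SE), to 0.10 gives n = 621.7, that is 622 cases and 1,244 controls.
- 622 × 1.2 / 0.5 = 1,493, rounded in the article to 1,500.

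The sample size is not in dispute. The 80% is a planning value for symptomatic disease, and the article itself says that effectiveness varies by variant.

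**Relation between the two quantities.** The risk of a severe outcome is the risk of becoming a symptomatic case times the risk of progression given that one is a case. Hence

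VE(severe) = 1 − (1 − VE(symptomatic)) × RR(progression).

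Inputs: VE(symptomatic) of 80% from Sample size; 50% and 30% as assumptions; progression relative risks of 0.5, 0.7 and 1.0 as assumptions. The article gives none of the assumed values.

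| Case-only RR (reduction among cases) | VE(symptomatic) 80% | 50% | 30% |
|---|---|---|---|
| 0.5 (50%) | 1 − 0.2 × 0.5 = 90% | 1 − 0.5 × 0.5 = 75% | 1 − 0.7 × 0.5 = 65% |
| 0.7 (30%) | 1 − 0.2 × 0.7 = 86% | 1 − 0.5 × 0.7 = 65% | 1 − 0.7 × 0.7 = 51% |
| 1.0 (0%) | 1 − 0.2 × 1.0 = 80% | 1 − 0.5 × 1.0 = 50% | 1 − 0.7 × 1.0 = 30% |

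The gap between the case-only reduction and effectiveness against the outcome is largest when protection against symptomatic disease is high. In the 0.5 row it falls from 40 points (90 − 50) to 25 (75 − 50) and then 15 (65 − 50); in the 1.0 row, from 80 points to 50 and then 30.

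The table takes the progression relative risk as free of the selection bias described above. With that bias, the case-only figure could also miss the true progression effect.

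**The case against.** The best defence is that nothing is hidden. The design is described as a test-negative study with follow-up of cases, Outcomes attaches the restriction to every severe outcome, and progression among cases is a legitimate question of clinical interest. That stands: the fault is the mismatch with the stated aim, not the case-only models themselves.

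Three stronger readings are tempting and are not supported.

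- *The protocol would report one minus the case-only relative risk as vaccine effectiveness.* It does not say so. The conversion from odds ratio to effectiveness is given for the primary analysis, whose model is extended only to infection outcomes. Severe outcomes stay as hazard ratios or relative risks, and the objectives speak of impact. The word effectiveness is tied to complications in the abstract.
- *The study cannot yield effectiveness against complications.* This is true of the planned analysis but not of the data. Vaccination status is collected at baseline for cases and controls, and under the test-negative assumptions the primary odds ratio and a case-only relative risk could be combined as above, although no such estimate or interval is planned.
- *A vaccine that works well will look useless.* This needs high protection against symptomatic disease together with little or no protection against progression. The article supports neither for the variants in circulation.

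It is also fair to say that a test-negative estimate for severe outcomes is imperfect. Controls are care-seekers with any listed symptom and are not followed, so severity and care setting would not be matched.

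The article calls secondary analyses exploratory, which limits the consequence. That label is given because there is no multiplicity adjustment; it does not tell the reader which quantity is being estimated.

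**Conclusion.** The point holds as a mismatch between aim and estimand. The abstract promises effectiveness against complications, and the objectives and Discussion speak of impact without restriction, while the only planned analysis of hospitalisation, ICU admission, ventilation and death estimates progression among symptomatic, care-seeking cases. The article does not warn that this leaves out protection through avoided illness or that it is open to selection bias.

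Over the range examined, effectiveness against the severe outcome exceeds the case-only reduction by between 15 points (relative risk 0.5 with 30% effectiveness against symptomatic disease) and 80 points (relative risk 1.0 with 80%). Only the 80% comes from the article. The result rests on the product relation and on a progression relative risk taken as unbiased.

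The primary analysis and the sample size are unaffected, and so are outcomes that make sense only among cases, such as symptom duration. The change should be made, but it does not threaten the study's main conclusion.

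**What to change.** 1. In Outcomes and Secondary outcome analyses, label the case-only models for the four severe outcomes *progression among symptomatic cases*. State that they are not effectiveness against the outcome, and add conditioning on infection to the limitations.
2. Then do one of the following.
   - Add, as an exploratory secondary analysis, a test-negative estimate for each severe outcome with enough events: cases who had the outcome against test-negative controls, in the primary logistic model, with VE = (1 − OR) × 100. Include a sensitivity comparison that uses controls already enrolled with an admitting diagnosis of respiratory illness.
   - Or reword the aim in the abstract, the secondary objectives and the Discussion to severity among cases.

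Cost: a few extra models on data already collected, with no new recruitment and no follow-up of controls. The price of the added estimate is wide intervals if severe events are few, and a caveat that the main control group is not matched on severity or care setting. The rewording option costs only text, but it gives up the claim about complications.

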### Study setting

This study has been conducted in Toledo (24° 42′ 50″ S, 53° 44′ 34″ W), a city in the state of Paraná, southern Brazil. The population of Toledo was estimated at 144,601 people in 2021. As of 05 February 2022, COVID-19 has affected 38,614 people with 478 deaths. The city secretary of health initiated an age-based COVID-19 vaccination campaign on 20 January 2021, starting with adults 16 years of age and older. A mass vaccination campaign using BNT162b2 for all nonimmunized individuals aged ≥ 12 years was initiated on 27 August 2021 using a two-dose schedule administered 21 days apart. A third dose (i.e., booster dose) of BNT162b2 has been recommended for healthy (according to an age-based prioritization strategy) and immunocompromised individuals aged ≥ 12 years since 15 September 2021. Other available COVID-19 vaccines in Toledo include CoronaVac (Sinovac), ChAdOx1 nCoV-19 (AstraZeneca), and Ad26.COV2.S (Janssen); around 50% of the vaccine-eligible individuals immunized against COVID-19 have received BNT162b2.

Toledo was chosen due to the city standard of care, which provides free healthcare access to a wide variety of COVID-19 diagnosis and management services, and due to the feasibility of accessing information on people who were tested for SARS-CoV-2 through the city surveillance system.

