#### Primary outcome analysis

The primary study analysis compares the vaccine effectiveness for symptomatic SARS-CoV-2 infection of participants vaccinated with two or more doses of BNT162b2 mRNA and participants never vaccinated. Logistic regression adjusted by age, gender, Charlson comorbidity index, BMI, and current smoking status will be used to estimate the odds ratio of vaccination among test positive cases and test negative controls. We also will incorporate in the model the time (number of days) elapsed between the study start and date of RT-PCR sample collection as a proxy of temporal trend. The reference group for vaccination status will be those who had not received a first vaccine dose before the date of sample collection. The estimate of vaccine effectiveness will be provided by 1 –odds ratio x 100 under the assumptions of a test negative design [20]. 95% CIs will be calculated using the Wald method.

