## Study status

The study design and protocol were finalised in October 2021. The first participant was included on November 3, 2021. At study start, approximately 2/3 of the target population was fully vaccinated. Two thousand and thirty-four participants were enrolled up to February 2, 2022. Currently, this study is recruiting participants in 3 referral COVID-19 sites in Toledo. We anticipate that the recruitment will be completed in July 2022.

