### Protocol review and amendments

#### Sample size review

According to the original sample size estimation, 2,979 participants (993 cases and 1,986 controls) would be required to detect an odds ratio ≤ 0.70 for the primary outcome analysis, assuming the recruitment of two controls per case, a rate of complete vaccination with the Pfizer-BioNTech BNT162b2 mRNA vaccine of 60% in the control group, a two-tailed alpha of 5%, a power of 80%, and an increased sample size by 30% (due to parameter uncertainties and need for covariate adjustment). In order to achieve adequate power to assess the impact of BNT162b2 on symptomatic SARS-CoV-2 infection associated with the Gamma variant (predominant SARS-COV-2 lineage at the time of study protocol development), considering a rate of 32.5% of genotyping tests with inconclusive results and a prevalence of 90% of the Gamma variant, the original sample size was determined to be 4,500 participants (1,500 cases and 3,000 controls).

In January 2022, the study sample size was revised, given the frequent variation of COVID-19 pandemic factors that could impact sample size estimation (e.g., emergence of Omicron variant, scarcity of new COVID-19 cases due to Gamma variant, increase in vaccine coverage, and vaccine effectiveness variations for distinct SARS-CoV-2 variants). Revision was made based solely on the number of recruited patients, number of cases and proportion of positive cases in the whole sample, without any additional analysis. The original study sample size (4,500 participants) was judged to provide an appropriate power to assess the primary outcome analysis as described in the sample size section.

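### The time-since-dose analysis is not variant-specific, so if effectiveness differs by variant its trend is confounded by the arrival of Omicron

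*Protocol article*

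**What the plan says.** All references are to the protocol article.

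- **The analysis.** Secondary outcome analyses announces "Crude and adjusted generalized linear models will be used to assess the impact of exposures" on a list of outcomes and, in the same sentence, "to test associations between length of time after receipt of the second or third dose of BNT162b2 and the risk of symptomatic SARS-CoV-2 infection". No variant is attached to that outcome, and no adjustment set is listed.
- **Where variants are meant, they are named.** The preceding paragraph of that section covers "The association between the exposition variables with symptomatic SARS-CoV-2 infection caused by circulating variants". It refers to the exposure variables, which the Exposures section defines as dose categories. Time since dose is not among them.
- **Calendar time.** The primary model carries "time (number of days) elapsed between the study start and date of RT-PCR sample collection as a proxy of temporal trend". Its functional form and any interaction with vaccination are not stated.
- **Dates.** Study setting says the BNT162b2 mass campaign "was initiated on 27 August 2021 using a two-dose schedule administered 21 days apart", and that third doses were recommended from 15 September 2021. Study status says "The first participant was included on November 3, 2021" and expects recruitment to end in July 2022.
- **Variants.** The January 2022 sample size review cites the emergence of Omicron and "vaccine effectiveness variations for distinct SARS-CoV-2 variants". The Introduction calls Omicron the most prevalent lineage at the time of writing. Variant identification says that every positive sample is typed.

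**The concern.** Time since dose and calendar time move together when doses start within a narrow window and enrolment follows. Here the dominant variant also changed during enrolment. If the vaccine protects less against the later variant, long intervals look worse than short ones even when protection against each variant is constant. The vaccine effect itself changes with the variant, so a calendar-time term shared by vaccinated and unvaccinated participants cannot absorb the change.

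At stake is what the study can say about duration of protection, which the Introduction names among the evidence gaps that motivate it. The Discussion's list of limitations does not mention this problem.

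**Working it through.** **1. Dates (from the article).** The earliest campaign second dose is 27 August 2021 + 21 days = 17 September 2021. The earliest third dose is 15 September 2021. If BNT162b2 was used from its approval on 11 June 2021, a second dose was possible from 2 July 2021 (+ 21 days). Longest possible interval in days:

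| On | Campaign dose 2 | Dose 3 | Dose 2 from 2 July |
|---|---|---|---|
| 3 Nov 2021 | 47 | 49 | 124 |
| 1 Jan 2022 | 106 | 108 | 183 |
| 2 Feb 2022 | 138 | 140 | 215 |
| 31 Jul 2022 | 317 | 319 | 394 |

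**2. Crude trend by hand, no waning.** Assumptions, none from the article:
- effectiveness 85% before and 50% from 1 January 2022 (odds ratios 0.15 and 0.50)
- positivity 33% in the unvaccinated, so odds 0.33/0.67 = 0.4925
- uniform enrolment from 3 November 2021 to 31 July 2022, 85% vaccinated
- dose 2 given from mid-September to early December 2021

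Under this pattern the share of records from 2022 is 33%, 98% and 100% at <90, 90-179 and ≥180 days.

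- Positivity in the vaccinated before 2022: odds 0.15 × 0.4925 = 0.0739, probability 0.0688.
- Positivity in the vaccinated in 2022: odds 0.50 × 0.4925 = 0.2463, probability 0.1976.
- <90 days: 0.67 × 0.0688 + 0.33 × 0.1976 = 0.1113; odds 0.1252; odds ratio 0.1252/0.4925 = 0.254; effectiveness 75%.
- 90-179 days: 0.02 × 0.0688 + 0.98 × 0.1976 = 0.1950; odds 0.2422; odds ratio 0.492; effectiveness 51%.
- ≥180 days: 50%.

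The crude fall from 75% to 50% comes entirely from the variant mix.

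**3. Adjusted models, by simulation, still with no waning.** Effectiveness (%) at <90, 90-179 and ≥180 days, with the unvaccinated as reference. Switch on 1 January 2022; 85% then 50%. Reruns agree within about 2 points.

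| Setting | Crude | Linear days | Two-week indicators | Omicron period only |
|---|---|---|---|---|
| Campaign dose 2, positivity 33% throughout | 74/49/50 | 71/49/54 | 69/55/52 | 50/49/50 |
| Campaign dose 2, positivity 45% then 65% | 79/41/40 | 71/40/58 | 69/58/53 | 50/50/50 |
| Dose 2 from 2 July 2021 | 76/61/50 | 71/58/55 | 68/60/56 | about 50 in each |

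Calendar adjustment falls short because the vaccine's log odds ratio shifts by ln(0.50/0.15) = 1.20 at the switch. That is an interaction, and a calendar main effect does not contain it.

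**4. Sensitivity.**
- *Smaller gap (80% v 65%), campaign dose 2:* crude 75/64/64, linear days 74/65/67.
- *Dose 3 given from 15 September 2021 to about May 2022, 85% v 50%, positivity 45% then 65%:* crude 58/41/40, linear days 56/50/58. If only 10% enrol before January, linear days gives 51/49/53.
- *Vaccinated participants only* (80% then 50%, campaign doses to 2 January 2022, positivity 45% then 65%): the odds ratio per 30 days is 1.14 crude, 0.93 with linear days and 1.00 with a variant-period term. The article does not say whether the unvaccinated enter this model.

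**The case against.** A reader might infer that long intervals can be seen only under Omicron, so that variant replacement is bound to be reported as waning. The documents do not support that.

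- **Earlier second doses are not excluded.** Approval is dated 11 June 2021, and the city's general campaign began on 20 January 2021. "A mass vaccination campaign using BNT162b2 for all nonimmunized individuals aged ≥ 12 years was initiated on 27 August 2021" does not say that BNT162b2 was unused before. No date of Omicron dominance is given; 1 January 2022 is an assumption.
- **The adjusted result need not look like waning.** With linear days, campaign dose 2 falls and then rebounds (71/40/58%), and the vaccinated-only slope points the other way (0.93).
- **Dose 3 is affected less** if boosters continue into 2022.
- **Enrolment was not uniform.** By 2 February 2022, 2,034 of 4,500 (45%) had been enrolled in 91 of about 270 days (34%). The split around 1 January is not reported.
- **Status.** Time since dose is not one of the nine secondary objectives, and secondary analyses are declared exploratory. The article is condensed, and a fuller plan might stratify.

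These points stand and limit the claim, but they do not remove it. The article expressly plans a crude model, where the false decline is clearest. It names variants in the neighbouring paragraph and not here. A fuller covariate list would not cure the problem where the unvaccinated are the reference. The exploratory label is tied to multiplicity and does not address systematic confounding.

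**Conclusion.** The point holds in a limited form. As written, the analysis relates time since dose 2 or 3 to infection by any variant. For campaign dose 2 and dose 3, intervals beyond about 106-108 days arise only from January 2022 on. If effectiveness differs by variant, as the sample size review allows, the trend mixes waning with variant replacement.

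Under an assumed drop from 85% to 50%, a crude model for campaign dose 2 can show an apparent fall of 24 to 39 points (74 − 50; 79 − 40) with no waning. Additive calendar adjustment leaves differences of up to 31 points between bands (71 − 40), not necessarily as a steady decline. With 80% v 65% the crude fall is 11 points (75 − 64), and for dose 3 the adjusted distortion is smaller. If effectiveness did not differ by variant, this mechanism would not operate. The primary analysis is outside this point. The change is worth making before analysis, but the trial does not depend on it.

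**What to change.** In Secondary outcome analyses, state that the time-since-dose analysis is run within variant, with calendar-time adjustment. That means Omicron-typed cases against controls sampled in the Omicron period, and Delta-typed cases against Delta-period controls where numbers allow. Alternatively, fit one model with a vaccination-by-variant-period interaction, with the periods defined from the study's own typing. State whether unvaccinated participants are included. Draw any conclusion on duration of protection from the within-variant estimate, and label a crude or pooled trend as not separable from variant replacement.

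The cost is a few lines of text and a stratified model on data already being collected. The downside is wider intervals and little information on long intervals before Omicron.

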### Study design

The present study is a test-negative case-control study with follow-up of cases (Fig 1). In this design, the same clinical case definition is used for both cases (i.e., participants with symptoms consistent with COVID-19) and controls (i.e., participants without the outcome) [11]. Reverse transcription polymerase chain reaction (RT-PCR) test for SARS-CoV-2 is prospectively used to distinguish cases from controls. Vaccination status and potential confounders are retrospectively ascertained among cases and controls through structured interviews and medical records review. Test-positive cases are prospectively followed through structured telephone interviews performed at 15 days, and at 1, 3, 6, 9 and 12 months.

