### Participants

The present study population is composed of consecutive individuals aged 12 years or older who seek the public healthcare system of Toledo with symptoms suggestive of COVID-19.

Inclusion criteria are (1) age ≥ 12 years old; (2) to be a resident of Toledo; (3) seeking care in the public healthcare system of Toledo with symptoms suggestive of COVID-19 defined as follows: acute respiratory infection symptoms (nasal congestion, rhinorrhea, anosmia, sore throat, hoarseness, new or increased-from-baseline cough, sputum production, dyspnea, wheezing, myalgia) OR admitting diagnosis suggestive of acute respiratory infection symptoms (pneumonia, upper respiratory infection, bronchitis, influenza, cough, asthma, viral respiratory illness, respiratory distress, respiratory failure), and (4) having a nasopharyngeal (NP) or nasal sample for SARS-CoV-2 diagnosis obtained as standard of care.

Patients with history of remdesivir treatment in the past 30 days, convalescent plasma treatment in the past 90 days, treatment with monoclonal antibodies for COVID-19 in the past 90 days (e.g., sotrovimab, casirivimab-imdevimab, bamlanivimab, etesivumab), and those who refused to provide informed consent are excluded. Participants are allowed to re-screen; however, the follow-up is performed considering only the first enrollment of each individual for the study.

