### Sample size

The sample size was calculated based on formulas published by O’Neill RT [9]. Assuming the recruitment of two controls per case, a vaccine coverage rate of 90% among controls, a sample of 622 cases and 1,244 controls will be required to detect a vaccine effectiveness of 80% with a precision width of 10%. Considering that around 50% of enrolled participants will fulfil criteria for the primary analysis (≥ 2 doses of BNT162b2 or unvaccinated) and increasing the sample size by 20% (due to parameter uncertainties, potential COVID-19 misclassifications, and need for covariate adjustment), the study will need to include 1,500 cases and 3,000 controls.

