### Data collection

The schedule of enrollment and assessment is detailed in Fig 2. Controls are evaluated at a single point in time (baseline). Cases are evaluated at baseline and then followed up for 12 months by means of structured telephone interviews at 15 days, and at 1, 3, 6, 9 and 12 months after inclusion in the study.

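### The time-since-dose analysis of infection falls under a rule that allows only hazard ratios or relative risks, although infection is the case-control status and the primary analysis uses the odds ratio

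*Protocol article*

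**What the plan says.** The article describes its design in one line: "The present study is a test-negative case-control study with follow-up of cases". Under Primary outcome analysis, vaccine effectiveness (VE) comes from logistic regression as one minus the odds ratio, times 100, with covariates and a term for days from study start to sample collection.

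Secondary outcome analyses has two paragraphs. The first sends the variant-specific outcomes and the secondary exposures to the primary model. The second uses crude and adjusted generalized linear models, chosen by the distribution of each outcome. It covers symptom duration, hospitalisation, ICU admission, ventilation, death, quality of life, persistent symptoms and reinfection among test-positive participants. The same sentence then adds a further purpose: "to test associations between length of time after receipt of the second or third dose of BNT162b2 and the risk of symptomatic SARS-CoV-2 infection". The paragraph closes: "Categorical outcomes will be expressed as hazard ratio or relative risk as appropriate". It does not list the odds ratio.

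Data collection states that controls are assessed at baseline only.

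**The concern.** The other outcomes in that second paragraph belong to a cohort of cases followed forward, and for the categorical ones a hazard ratio or relative risk is legitimate. Time since dose against symptomatic infection is different. Its outcome is the RT-PCR result that divides the sample into cases and controls, so the information can come only from the case-control contrast.

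Neither listed measure fits that contrast. Controls contribute no follow-up, so there is no time at risk from which to model a hazard of infection. The proportion testing positive is not a population risk either. Enrolment takes "consecutive individuals aged 12 years or older who seek the public healthcare system of Toledo with symptoms suggestive of COVID-19", so that proportion moves with SARS-CoV-2 activity and with other respiratory illness. A ratio of such proportions changes with the mix of cases and controls even when the vaccine effect is constant.

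At stake is the article's only stated analysis of how protection changes with time since vaccination. The Introduction names long-term protection as an evidence gap.

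**Working it through.** **1. The plan's own figure, to establish its scale.** Inputs from Sample size: "Assuming the recruitment of two controls per case, a vaccine coverage rate of 90% among controls", VE 80% (odds ratio 0.20), precision width 10%. The 95% confidence level is from Overall principles.

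- Exposure odds in cases = (0.90/0.10) × 0.20 = 1.8, so p1 = 1.8/2.8 = 0.643.
- V = 1/(p1(1 − p1)) + 1/(2 × 0.90 × 0.10) = 4.356 + 5.556 = 9.911.
- A full interval width of 0.10 on the odds-ratio scale requires a half-width d on the log scale with 2 × 0.20 × sinh(d) = 0.10, so d = asinh(0.25) = 0.2475.
- n = 9.911 × (1.96/0.2475)² = 621.7, rounded up to 622 cases and 1,244 controls.

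This matches the article exactly. The sample size is built on the odds ratio.

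**2. What a relative risk would do to a late-versus-early comparison.** Let k be the number of controls per case, f the share of vaccinated controls who are late after their dose, and OR the true late-versus-early odds ratio. The article gives neither f nor OR, so both are assumed: f = 0.5 and OR = 3.

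- Share late among cases: g = f·OR/(f·OR + 1 − f) = 1.5/2.0 = 0.75.
- Positive fraction, late: g/(g + k·f). Positive fraction, early: (1 − g)/((1 − g) + k(1 − f)).
- Sample relative risk = late fraction divided by early fraction.
- Sample odds ratio = g(1 − f)/((1 − g)f) = 0.375/0.125 = 3. Here k cancels.

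| Controls per case (k) | Positive, late | Positive, early | Relative risk | Odds ratio |
|---|---|---|---|---|
| 0.5 | 0.75/1.00 = 0.750 | 0.25/0.50 = 0.500 | 1.50 | 3.00 |
| 1 | 0.75/1.25 = 0.600 | 0.25/0.75 = 0.333 | 1.80 | 3.00 |
| 2 (planned) | 0.75/1.75 = 0.429 | 0.25/1.25 = 0.200 | 2.14 | 3.00 |
| 4 | 0.75/2.75 = 0.273 | 0.25/2.25 = 0.111 | 2.45 | 3.00 |

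With a true odds ratio of 2 and the same split, the relative risks are 1.27, 1.43, 1.60 and 1.75. In both sets the relative risk lies nearer to 1 than the odds ratio, and the gap widens as positivity rises. At the planned ratio one participant in three is positive (1/(1 + 2)), so the outcome is too common in the sample for the two measures to be interchangeable.

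**3. The two passages side by side.** Primary outcome analysis gives an odds ratio for vaccination against test result. The second paragraph of Secondary outcome analyses gives a hazard ratio or relative risk for time since vaccination against the same test result. Only the first suits the sampling.

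**The case against.** The strongest reply is that no wrong model is actually fixed. Logistic regression is a generalized linear model and the natural one for a binary outcome. No link function is named. The sentence on effect measures is a blanket one, written mainly for the outcomes in cases, and its closing qualifier leaves some room. Under the test-negative assumptions that the article invokes, the odds ratio is read as the relative measure behind VE, so relative risk may be loose wording for it. This stands in part: the bias is conditional on a relative risk being modelled directly. It does not remove the conflict. The other infection analyses were explicitly routed to the primary model and this one was not, and the qualifier chooses between two measures that both fail here. Because a measure is stated, this is not detail left to a fuller plan.

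A reader might go further in three ways that the article does not support.

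- **That VE itself will be reported wrongly.** At 90% coverage in controls, a relative risk would turn a true VE of 80% into 58.9% with two controls per case (46.7% with one, 67.9% with four). Those figures describe vaccinated against unvaccinated, which the plan analyses with the odds ratio. The time-since-dose clause names no unvaccinated reference and promises no VE.
- **That calendar time is omitted, so variant replacement would pass for waning.** The article lists no covariates for any model in that paragraph, and an article may leave these to the full plan. Silence does not show omission.
- **That time since dose runs almost in step with calendar date.** The BNT162b2 mass campaign "was initiated on 27 August 2021 using a two-dose schedule administered 21 days apart", but it was aimed at people not yet immunized, and boosters from 15 September 2021 restart the clock at varying dates. Some correlation is plausible; its strength cannot be derived from the article.

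**Conclusion.** The concern holds as a misassigned effect measure. As written, the time-since-dose analysis of symptomatic infection may be expressed only as a hazard ratio, which cannot be modelled without follow-up of controls, or as a relative risk, which depends on the ratio of controls to cases. This contradicts the odds-ratio approach of the primary analysis. If a relative risk were fitted, waning would be understated: a true late-versus-early odds ratio of 3 would appear as 2.14 at the planned ratio, with a range of 1.80 to 2.45 between one and four controls per case. These values rest on the assumed even split of controls and the assumed true odds ratio. The direction toward the null does not depend on them.

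Severity is moderate. The analysis is a single clause, is not among the listed secondary objectives, and falls under the article's statement that secondary analyses are exploratory. That label is given in the context of multiplicity and does not make an unsuitable measure valid. The primary estimate is unaffected.

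**What to change.** Make two changes of wording in Secondary outcome analyses.

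1. Move time since the second or third dose into the first paragraph, so that it uses the primary logistic model with its covariates and calendar-time term. Report the odds ratio, and VE as (1 − OR) × 100 where the reference group is unvaccinated.
2. Limit the sentence on hazard ratio and relative risk to outcomes followed among test-positive cases.

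No new data are needed: the exposure definitions already require the timing of doses relative to symptom onset, and the primary model already uses the sample date. If results are given by time band, the price is wider intervals within each band. Time bands, flexible calendar terms and stratification by variant are optional refinements and are not needed to correct the error.
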